**Potential variables will be collected on consenting/assenting patients:**

- Survey-collected data (patient report):
  - Gender identity
  - Age
  - Race
  - Gender
  - Ethnicity
  - Treatment/disease status
- Medical record extraction
  - Clinic/site
  - Presence/absence and type of endocrinopathy
  - Exposure and dose of alkylator chemotherapy
  - Prior history of spinal, pelvic or testicular radiation
  - Prior history of spinal or pelvic surgery
  - Documentation of sexual function concerns (before and after screening)
  - Treatment for sexual function concerns (before and after screening)

## **8.2 ADVERSE EVENTS AND SERIOUS ADVERSE EVENTS**

### **8.2.1 Definition of Adverse Events (AE)**

**Adverse event** means any untoward medical occurrence associated with the use of an intervention in humans, whether or not considered intervention-related.

### **8.2.2 Definition of Serious Adverse Events (SAE)**

**Serious adverse event** or **serious suspected adverse reaction**. An AE or suspected adverse reaction is considered “serious” if, in the view of either the investigator or sponsor, it results in any of the following outcomes: death, a life-threatening adverse event, inpatient hospitalization or prolongation of existing hospitalization, a persistent or significant incapacity or substantial disruption of the ability to conduct normal life functions, or a congenital anomaly/ birth defect. Important medical events that may not result in death, be life-threatening, or require hospitalization may be considered serious when, based upon appropriate medical judgment, they may jeopardize the patient or subject and may require medical or surgical intervention to prevent one of the outcomes listed in this definition.

### **8.2.3 CLASSIFICATION OF AN ADVERSE EVENT**

### **8.2.3.1 severity of event**

For AEs, the following guidelines will be used to describe severity.

- **Mild** – Events require minimal or no treatment and do not interfere with the participant’s daily activities.
- **Moderate** – Events result in a low level of inconvenience or concern with the therapeutic measures. Moderate events may cause some interference with functioning.
- **Severe** – Events interrupt a participant’s usual daily activity and may require systemic drug therapy or other treatment. Severe events are usually potentially life-threatening or incapacitating.

| Grade Severity | |
| --- | --- |
| 1. Mild; asymptomatic or mild symptoms; clinical or diagnostic observations only; or intervention not indicated 2. Moderate; minimal, local, or non-invasive intervention indicated; or limiting age-appropriate instrumental activities of daily living a 3. Severe or medically significant, but not immediately life-threatening; hospitalization or prolongation of hospitalization indicated; disabling; or limiting self-care activities of daily living b,c 4. Life-threatening consequences or urgent intervention indicated 5. Death related to adverse event |  |

NCI CTCAE  National Cancer Institute Common Terminology Criteria for Adverse Events. Note: Based on the most recent version of NCI CTCAE (v5.0), which can be found at: <http://ctep.cancer.gov/protocolDevelopment/electronic_applications/ctc.htm>

a Instrumental activities of daily living refer to preparing meals, shopping for groceries or clothes, using the telephone, managing money, etc.

b Examples of self-care activities of daily living include bathing, dressing and undressing, feeding oneself, using the toilet, and taking medications, as performed by patients who are not bedridden.

c If an event is assessed as a "significant medical event," it must be reported as a serious adverse event.

### **8.2.3.2 Relationship to Study INTERVENTION**

Only adverse events directly related to study intervention will be recorded.

### **8.2.3.3 Expectedness**

Expectedness will only be documented for SAEs. The PI will be responsible for determining whether an SAE is expected or unexpected. An SAE will be considered unexpected if the nature, severity, or frequency of the event is not consistent with the risk information previously described for the study intervention.

### **8.2.4 time period and frequency for event assessment and follow-up**

The occurrence of an AE or SAE may come to the attention of study personnel during study visits and interviews of a study participant presenting for medical care, or upon review by a study monitor. All AEs including local and systemic reactions not meeting the criteria for SAEs will be captured on the appropriate CRF. Information to be collected includes event description, time of onset, clinician’s assessment of severity, (if applicable) relationship to study intervention (assessed only by those with the training and authority to make a diagnosis), and time of resolution/ stabilization of the event. All AEs occurring while on study must be documented appropriately. All AEs will be followed to adequate resolution.

Any medical condition that is present at the time that the participant is screened will be considered as baseline and not reported as an AE. However, if the study participant’s condition deteriorates at any time during the study, it will be recorded as an AE. UAPs will be recorded in the data collection system throughout the study.

Changes in the severity of an AE will be documented to allow an assessment of the duration of the event at each level of severity to be performed. AEs characterized as intermittent require documentation of onset and duration of each episode.

The PI will record all reportable events with start dates occurring any time after informed consent/assent is obtained until 30 days after the last day of study treatment or until initiation of new treatment, whichever comes first. SAEs will be followed until resolution or stabilization. At each study visit, the investigator will inquire about the occurrence of AE/ SAEs since the last visit.

### **8.2.5 Adverse Event Reporting**

The investigator must record non-serious adverse events and report to DSMC and IRB according to timetable for reporting specified in section 10.1.6.

### **8.2.6 serious adverse event reporting**

The investigator must record all serious adverse events and report to DSMC and IRB according to timetable for reporting specified in section 10.1.5. Per institutional policy, all serious adverse events occurring at UCCC/UCHealth will be entered into OnCore according to timetable for reporting specified in section 10.1.5.

All SAEs will be reported using the FDA 3500A Mandatory MedWatch report form unless funding sponsor or drug manufacturer requires use of proprietary form. SAE form can be found at: <http://www.fda.gov/downloads/AboutFDA/ReportsManualsForms/Forms/UCM048334.pdf>

To submit an SAE, email as follows within 24 hours of becoming aware of the event:

To: [contact]

[[contact]](mailto:[contact])

[[contact]](mailto:[contact])

Subject: 22-0709 SAE Report Form

Attach: SAE form completed and signed by the Investigator

**Follow-up of unresolved serious adverse events**

Any SAEs that are unresolved at the time of the initial report submission should be followed up by the investigator for as long as medically indicated, and an updated SAE report submitted at the time new information regarding the event becomes available.

## **8.3 UNANTICIPATED PROBLEMS**

### **8.3.1 Definition of Unanticipated Problems (UAP)**

The Office of Human Research Protection (OHRP) considers unanticipated problems involving risks to participants or others to include, in general, any incident, experience, or outcome that meets **all** of the following criteria:

- Unexpected in terms of nature, severity, or frequency given (a) the research procedures that are described in the protocol-related documents, such as the IRB-approved research protocol and informed consent/assent document; and (b) the characteristics of the participant population being studied;
- Related or possibly related to participation in the research (“possibly related” means there is a reasonable possibility that the incident, experience, or outcome may have been caused by the procedures involved in the research); and
- Suggests that the research places participants or others at a greater risk of harm (including physical, psychological, economic, or social harm) than was previously known or recognized.

This study will use the OHRP definition of UAP.

### **8.3.2 REPORTING of Unanticipated Problems**

Incidents or events that meet the OHRP criteria for UAPs require the creation and completion of a UAP report. It is the Site PI’s responsibility to report UAPs to their IRB. The Lead PI is responsible for reporting the UAP to the IRB and the UCCC DSMC. The UAP report will include the following information:

- Protocol-identifying information: protocol title and number, PI’s name, and the IRB project number;
- A detailed description of the event, incident, experience, or outcome;
- An explanation of the basis for determining that the event, incident, experience, or outcome represents a UAP;
- A description of any changes to the protocol or other corrective actions that have been taken or are proposed in response to the UAP.

# 9 statistical considerations

## **9.1 Aim 1 Statistical plan**

**Aim 1. Develop and refine a routine, standardized SD screening approach for implementation in a pediatric oncology clinic using stakeholder input and iterative design.**

Endpoints

Analytic Plan: Facilitators and barriers identified in quantitative surveys and qualitative interviews will be integrated by mapping to the CFIR framework in a team approach (PI, methods mentors and qualitative research assistant). Initial deductive rapid coding will be performed by the research team via listening to recordings while completing the summary template and following a coding guide. This approach uses characteristics and content of language to provide understanding of qualitative data through systematic classification, coding, and theme identification. Coding will involve interpreting and assigning data into the Consolidated Framework for Implementation Research (CFIR) coding schema; for example, “lack of time” will be coded as an “inner setting barrier.” To enhance rigor, the two members of the research team will each independently review an initial set of recordings and meet to compare results and resolve discrepancies. This process will continue until discrepancies are minimal, at which point the research team will independently code the remainder of recordings. Results will inform modifications to the screening approach by the research team, informed by stakeholder recommendations and use of the CFIR-ERIC (Expert Recommendations for Implementing Change) matching tool, which links CFIR barriers with implementation strategies to mitigate these barriers. Based on recommendations in the literature, we expect that this process will require 3-5 rounds of iterative modifications addressing stakeholder feedback. Three stopping criteria will be used: (1) saturation in key informant interviews (no new unaddressed barriers/facilitators); (2) survey results indicate at least 80% acceptability, feasibility and appropriateness of the screening approach; and (3) stakeholders will identify no major problems with the screening approach (defined as those which would severely limit the ability of end-users to implement the screen approach). Once stopping rules are met, the research team will produce a draft screening approach and implementation package (e.g., use of a “clinical champion”, provider training, use of reminders in the electronic health record (EHR)). If the stopping rules have not been met after 5 rounds, the research team will decide upon the screening approach protocol and implementation package based on all elicited feedback. Changes will be documented in a “development document,” including dates, explanations, and discussion notes. Iterative changes will continue via the above process, with attention paid to preferences by sex/gender. The digital recordings will be later transcribed, and the same qualitative team will analyze transcripts using formal content analysis, which will further guide implementation planning. Finally, a stakeholder focus group (Appendix 4), recruited from prior medical stakeholders, will be convened to review the draft screening approach protocol. Following this final feedback elicitation, the research team will produce the final screening approach protocol, implementation materials, and a Fidelity Checklist.

Sample Size: We anticipate 3-5 rounds of pretesting and modification over 6 months, with each round consisting of 3-5 patient interviews, 3 medical stakeholder surveys, and 1 medical stakeholder interview (total unique patients=9-25, medical stakeholder surveys=9-15 and interviews=3-5). There are 9 eligible providers, 3 eligible nurses and 1 eligible MA; over the course of Aim 1, we will attempt to survey all providers/nurses/MAs at least once and perform interviews across each provider type. Though there is no consensus in the user-centered design literature on required sample size, we anticipate that our planned total sample size (n=27-51) for the iterative feedback and modification process, combined with our stopping criteria, are sufficient for our purpose and scope. For the final stakeholder focus group, we will 6 neuro-oncology medical stakeholders with at least 1 each of provider, RN, MA.

## **9.2 AIM 2 Statistical plan**

**Aim 2. Evaluate the preliminary effectiveness of the standardized screening approach for SD on occurrence of patient-provider SD communication.**

Analytic Plan: Descriptive statistics (means, medians, standard deviations, frequencies) will be computed for patient characteristics, overall and stratified by study period. Differences in patient predictors between study periods will be assessed using chi-squared and t-tests (or appropriate bivariable tests based on variable type and distribution).

The primary analysis will compare the effect of the intervention on the proportion of patients that self-report SD screening. We will use a multivariable logistic regression model for the binary outcome of self-reported SD screening, controlling for patient-level predictors identified a priori to be potential confounders (e.g., age, gender, presence of SD concerns, endocrinopathies, clinic site, on therapy or survivor). Although there is correlation due to the hierarchical structure of the data (patients within sites), due to the limited number of sites (<5), we will include a fixed effect for site rather than a random effect. The specific model will be of the form:

η_i_ = β_0_ + β_1_T_i_ + β_2_’Z_i_, (1)

where η_i_= log (ϕ_i_/ (1 - ϕ_i_)), is the log odds of success for patient i (i.e., patient i self-reported SD screening), T_i_ is an indicator of whether the measurement was taken in the pre-intervention (T_i_=0) or post-intervention (T_i_=1) period, Z_i_ is a vector of patient-level predictors including the site at which they were seen. To assess the intervention effect, we test the null hypothesis H_0_: β_1_=0 vs. H_1_: β_1_ ≠ 0. We will perform a subgroup analysis by key variables (site, therapy/survivor status) using an interaction between the subgroup variable and the intervention period. The secondary outcome of whether a patient reported that their SD need was met will be analyzed similarly, overall and in the subgroup of those that indicated that they had an SD need, which will be assessed using an interaction with the SD need indicator and the pre-/post- indicator.

We will also use similar multivariable regression models adjusted for the same covariates to assess the effect of the intervention on secondary and exploratory outcomes. The secondary outcome of patient satisfaction measured on a 0-10 scale will be modelled as a continuous outcome using a multivariable linear regression model. The exploratory outcome of feasibility of collecting EHR data will be modelled as a binary outcome (yes/no documented/detected SD) using a logistic regression model. The exploratory outcome of number of referral patterns will be modelled as a count outcome using a multivariable Poisson regression model. To examine whether the intervention effect differs by key variables (site, therapy/survivor status) we will assess for an interaction effect between study period (pre/post) and the variable.

Goodness-of-fit tests and model-fitting diagnostics will be performed for proposed analyses to assess for influential points, outliers, and to evaluate alternative model specifications. All hypothesis tests will be two-sided with alpha=0.05, and p-values and confidence intervals will be reported. Statistical analyses will be conducted using R or SAS version 9.4 (SAS Institute Inc., Cary, N.C.).

Power: Sample size calculations are based on the number of participants needed pre- and post-implementation of the screening approach to detect a 25% difference in proportion of patients reporting SD conversations with their providers (5% pre-intervention vs. 30% post-intervention), aggregated across all sites. Assuming a multivariable logistic regression in which 20% of the variability in the independent variable is explained by the other predictors, to detect a clinically relevant difference of 25% (5% pre-intervention vs. 30% post-intervention) in SD conversations with a two-sided test, 80% power, and alpha =.05, 86 participants will be required (43 pre- and 43 post-implementation of screening approach).

This power calculation is based on the following assumptions: 1) Pre-implementation, we anticipate 5% of participants will report having had an SD conversation with their providers (conservative, based on prior literature). 2) Post-implementation, we estimate that 30% of patients will report an SD conversation with their provider (conservative, based on (a) estimated SD prevalence rates of 20-50% and (b) the assumption that some patients/providers will initiate conversations regardless of SexFS Brief results). Assuming a conservative 50% response rate and approximately 38 eligible patients per month (derived from 2019 clinical volume), we anticipate that recruiting 43 patients for each study period will require approximately 3 months (0.5*38*3=57).

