# 3 OBJECTIVES AND ENDPOINTS

| **Aim** | **OBJECTIVES** | **ENDPOINTS** |
| --- | --- | --- |
| **1** | **Primary:** Iteratively test and refine a routine standardized SD screening and implementation approach in a pediatric oncology clinic using stakeholder input | Development of a refined screening approach after 3-5 rounds of iterative testing and modifications, as defined by three stopping criteria:  1) Saturation in key informant interviews regarding identified barriers/facilitators (i.e., no new unaddressed barriers/facilitators identified)  2) At least 80% of each group of stakeholders (patient, medical) surveyed will have scores of 4 or higher on the AIM, FIM, and IAM (indicating an average response of “agreeing” or “strongly agreeing” to items assessing the acceptability, feasibility, and appropriateness of the screening approach)  3) Stakeholders will identify no major problems with the screening approach (note that in the user-centered design field, “major problems” are defined as those which would severely limit the ability of end-users to implement the screen approach). |
|  | **Secondary:** To develop an implementation package for use of the routine screening approach developed as a primary objective. | Implementation package/materials for use of the routine screening approach developed as a primary objective. |
| **2** | **Primary**: Evaluate the preliminary effectiveness of the standardized screening approach for SD (developed in Aim 1) on occurrence of patient-provider SD communication, as measured by the rate of patient-reported SD conversations with providers. | Comparison of pre- and post- results of a patient-reported indicator that his/her provider has communicated with them about SD |
|  | **Secondary**: Evaluate secondary measures of effectiveness, including patient satisfaction, needs being met | Comparison of pre- and post- results patient satisfaction with SD communication, patient-report that an SD need was met |
|  | **Exploratory/Feasibility:** Feasibility of collecting EHR data to evaluate effectiveness of SD screening intervention | Incidence of documented/detected SD, number of referrals to SD-related specialty care via EHR order or note documentation |

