**Data Collection/Outcomes*:***

*Effectiveness*: Data will be collected prospectively on patients during the 3-month pre-intervention phase (n=43) and patients who receive SD screening within 1 month of it being due during the 3-month post-intervention phase (n=43) (total n=86). Additional data will be collected EHR, including documentation of and referrals for SD. Participants will complete a survey (Appendix 5) at the end of scheduled visits or via phone within 4 weeks of screening completion. The **primary outcome** is a patient-reported indicator that his/her provider has communicated with them about SD. We anticipate that most providers will only address SD with patients who report a concern on the SexFS Brief; this assumption is reflected in sample size calculations. However, because our preliminary work demonstrated that patients wanted SD conversations to accompany the SexFS Brief, our analysis will include all patients, regardless of SD screening results. **Secondary outcomes**, detailed in section 3, include patient satisfaction with SD communication^51^ and patient-report that an SD need was met. We will also assess the feasibility of collecting EHR data in all eligible patients via retrospective chart review (exploratory outcomes):

- Clinic/site
- Incidence of documented/detected SD
- Referral patterns to SD-related specialty care (fertility team, urology, gynecology/oncology, sexual health clinic, endocrinology, etc.) via EHR order or note documentation **(exploratory outcomes)**.

These secondary and exploratory outcomes will inform a future multicenter trial defining the clinical impact of our screening intervention. Brief demographic data will also be collected for each participant.

*RE-AIM Outcomes:* Data will be collected using a combination of quantitative patient (Appendix 5) and medical provider surveys (Appendix 6) purposive qualitative interviews with medical stakeholders, and research personnel observation (Appendix 7 and 8).^2,52^ For sites that choose to have a limited number of providers responsible for survey delivery and follow-up/management, only responsible providers will receive complete surveys. Surveys will be administered in person by the RA. Interviews will be completed in person or via telephone by the study’s qualitative RA using CFIR interview guides, similar to Aim 1.^48^

Details on assessment:

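### Section 9.2 models self-reported SD screening as the Aim 2 primary outcome, while the objective, endpoint, procedures and power calculation all use a patient-reported SD conversation with a provider

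*Protocol*

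**What the plan says.** The Aim 2 objective in section 3 is to be judged "as measured by the rate of patient-reported SD conversations with providers", and the matching endpoint is "Comparison of pre- and post- results of a patient-reported indicator that his/her provider has communicated with them about SD". The synopsis (section 1.1) has the same objective and endpoint. The overview table in section 4.1 lists a conversation with a provider as the primary outcome. In section 8.1 the primary outcome "is a patient-reported indicator that his/her provider has communicated with them about SD".

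The power paragraph of section 9.2 follows suit: the study is sized to "detect a 25% difference in proportion of patients reporting SD conversations with their providers", from 5% to 30%.

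The analytic plan in the same section uses another label. It opens with "The primary analysis will compare the effect of the intervention on the proportion of patients that self-report SD screening", continues with "We will use a multivariable logistic regression model for the binary outcome of self-reported SD screening", and defines success in equation (1) as "patient i self-reported SD screening".

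**The concern.** In this protocol, SD screening ordinarily means administering the SexFS Brief, which is the intervention (sections 1.1 and 6.1.1). Whether it was completed is the Aim 3 reach outcome (sections 6.2 and 8.1). A conversation with a provider is a later and separate event. Section 8.1 says so in substance: most providers are expected to raise SD only with patients who report a concern on the questionnaire, and the sample size is said to reflect this.

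A model whose success is a report of having been screened therefore estimates something close to delivery of the intervention. Its coefficient for study period could differ from zero while conversations stayed where they were, and the 5% and 30% planning rates would not describe the modelled outcome. The protocol also leaves two candidate primary analyses, with room to choose between them after the data are seen.

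**Working it through.** **Step 1. Outcome by location.**

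| Place in protocol | Outcome named |
| --- | --- |
| 1.1 Synopsis, Aim 2 objective and endpoint | Conversation / communication with provider |
| 3 Objectives and endpoints | Conversation / communication with provider |
| 4.1 Overview table | Conversation with provider |
| 8.1 Effectiveness outcomes | Communication by provider |
| 9.2 Power and its assumptions | Conversation with provider |
| 9.2 Primary analysis, first sentence | Self-reported screening |
| 9.2 Regression outcome | Self-reported screening |
| 9.2 Success in equation (1) | Self-reported screening |

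The mismatch needs no assumption.

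**Step 2. Which outcome does the sample size belong to?** Inputs from section 9.2: p1 = 0.05, p2 = 0.30, two-sided alpha 0.05, power 80%, 20% of the variability in the independent variable explained by the other predictors, 43 per period. The formula is not named. The pooled two-proportion form, inflated by 1/(1 − R²), comes close:

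n = [1.96·√(2p̄(1−p̄)) + 0.8416·√(p1(1−p1)+p2(1−p2))]² / (p2−p1)², with p̄ = 0.175

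= (1.0532 + 0.4271)² / 0.0625 = 35.06 per period

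Total 70.1; 70.1 / 0.8 = 87.6, so 88 against the stated 86. In reverse, the effective n is 43 × 0.8 = 34.4 per period, and

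power = Φ{[(p2−p1)·√34.4 − 1.96·√(2p̄(1−p̄))] / √(p1(1−p1)+p2(1−p2))}

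= Φ{(1.4663 − 1.0532) / 0.5074} = Φ(0.814) = 79.2%

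The stated figure is reproduced to within two participants, for the conversation outcome.

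**Step 3. How far apart can the two outcomes be?** At the planned 30% conversation rate, 43 × 0.70 = 30.1. If all 43 post-period patients had been screened, about 30 would have been screened without a conversation. They are failures under section 3 and, if they report the screening, successes under equation (1).

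**Step 4. Rejection probability for the outcome as written.** The protocol gives no rates for self-reported screening, so those below are assumptions. Same formula, 34.4 effective per period:

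| Assumed pre | Assumed post | Power |
| --- | --- | --- |
| 30% | 50% | 39.3% |
| 30% | 60% | 71.5% |
| 20% | 60% | 94.1% |
| 10% | 50% | 96.8% |
| 5% | 50% | 99.5% |
| 30% | 80% | 99.5% |

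For example, 30% versus 60% gives Φ{(1.7595 − 1.3790) / 0.6708} = Φ(0.567) = 71.5%, and 5% versus 50% gives Φ{(2.6393 − 1.2377) / 0.5454} = Φ(2.570) = 99.5%. None of these depends on the conversation rate; they would be the same if conversations did not change at all.

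**Step 5. Who is in the post-period sample?** The outcome paragraph of section 8.1 describes patients screened within 1 month of the due date. Section 5.4 also recruits patients whose screening is overdue by 4 weeks or more, and gives the effectiveness part of the survey to every participant. Section 5.1 excludes unscreened patients from Aim 3 outcomes only. The post-period rate of reported screening depends heavily on which description applies.

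**The case against.** The strongest reply is that this is loose wording. The Aim 2 title directly above the analytic plan speaks of patient-provider communication, and the power text in the same section assumes a logistic regression on conversations. Section 2.2 itself describes clinicians' infrequent discussion of sexual function as a low rate of screening. Section 5.4 limits the pre-period survey to communication and clinical care, and no listed effectiveness item asks whether a questionnaire was completed. The survey (Appendix 5) is not available here. A slip is therefore plausible, and the intended analysis may well be the right one.

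That lowers the likely damage but does not remove the contradiction. The label is used consistently three times, once inside the model definition that an analyst would program from, and nothing in section 9.2 equates the two events.

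A reader might go further and infer that a positive result is all but certain, that nearly every post-period patient would count as a success, or that the fit would be quasi-separated. The documents do not support this. They give no reporting rates, the survey item cannot be seen, and sections 5.1 and 5.4 point to unscreened patients being in the effectiveness sample. Some assumed rates give only moderate power (Step 4).

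**Conclusion.** The primary analysis in section 9.2 is wrong as written: it names an outcome that differs from the protocol's own objective, endpoint, procedures and power calculation. This rests on the text alone and should be corrected before any analysis.

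The consequence is conditional. Run literally, the model could reject the null hypothesis through delivery of the questionnaire with no change in conversations, and the 5% and 30% rates would not apply to it. The probability of that depends on assumed reporting rates and on the unresolved post-period sample. The illustrations of 71.5% (30% versus 60%) and 99.5% (5% versus 50%) are not bounds. With the conversation outcome restored, 86 participants give about 79% power under the plan's own assumptions, so this point does not affect the sample size.

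**What to change.** In section 9.2, replace self-reported SD screening in the opening sentence of the primary analysis, in the regression outcome and in the definition of success for equation (1). The replacement is the section 8.1 outcome, "a patient-reported indicator that his/her provider has communicated with them about SD", taken from the same survey item in both periods. Add that completing the SexFS Brief does not by itself count as a conversation.

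Reconcile sections 5.4 and 8.1 on whether patients overdue for screening belong to the post-period effectiveness sample, and carry the answer into section 9.2.

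There is no reason to retain self-reported screening as an Aim 3 delivery measure: the protocol lists none, and reach already comes from record abstraction.

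The cost is an amendment to wording. The sample size need not change, and no extra data are needed provided the survey already carries the communication item in both periods, as sections 5.4 and 8.1 indicate.
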